**Financial administration:**

Funding for this study, will come from the UBC account 20R 54590 into which donations and honoraria are placed. There continues to be in kind contribution of drug and placebo for Prometrium® from Schering, Canada. This company does not control the conduct of the study.

**Introduction:**

Menopausal women often need or desire therapy to deal with night sweats or hot flashes (commonly vasomotor symptoms [VMS]). With the current evidence that estrogen with low dose progestin therapy increases the risk for pulmonary embolism, heart attacks, strokes and breast cancer (WHI 2002), women are increasingly reluctant to take it.

Progesterone and progestins are known to be effective in decreasing VMS (Albrecht, Schiff, Tulchinsky, & Ryan, 1981; Lobo, McCormick, Singer, & Roy, 1984; Paterson, 1982; Quella et al., 1998). In addition, oral micronized progesterone (Prometrium®,OMP), in a double blind randomized placebo controlled sleep study in men, increases deep sleep by 15% (Friess, Tagaya, Trachsel, Holsboer, & Rupprecht, 1997). OMP, like medroxyprogesterone ([name], Alojado, McKay, & Vigna, 1994), is well-tolerated by menopausal women (Moyer, de Lignieres, Driguez, & Pierre, 1993). Furthermore, non-androgenic progestins do not appear to increase the risk for venous thromboembolic disease nor breast cancers, although no long safety trial has specifically tested oral micronized progesterone (OMP, Prometrium) versus placebo. Furthermore, no placebo-controlled trial has tested OMP for VMS in menopausal women.

Women who decide to take medications for menopause and osteoporosis prophylaxis would like to know that they are also decreasing their risks for cardiovascular disease (CVD). One of the more physiological of the CVD risk indicators is abnormal function of the vascular endothelial nitric oxide system. Preliminary data in a randomized cross-over vehicle-controlled trial of intra-arterial infusion of progesterone suggests that it is similar to (or stronger than) estrogen in increasing endothelial function (Mather, [name], [name], & [name], 2000). Progesterone also decreases blood pressure (Rylance et al., 1985) and is likely to decrease weight (because of its effect to increase core temperature and metabolic rate).

**Purposes:**

The purposes of this three-month randomized double-blind placebo-controlled trial in menopausal women without risks for cardiovascular disease and with moderate VMS at baseline are:

1. To determine whether full dose daily oral micronized progesterone (OMP) increases forearm blood flow in response to infusion of acetylcholine;
2. **T**o determine, compared with a month’s pre-treatment record, whether and by how much day and night VMS will change in response to treatment with OMP or placebo;
3. **T**o determine whether OMP has any effects on change in lipids and BP compared with placebo.

**Null Hypotheses:**

1. Progesterone for three months will not increase endothelium-dependent forearm blood flow in response to acetylcholine infusion compared with the baseline before therapy or compared with placebo treatment.
2. Progesterone for three months to menopausal women with existing moderate day and night vasomotor symptoms will cause no change in VMS over time compared with placebo.
3. Hormone related quality of life (as documented by the Daily Menopause Diary) will not differ between those randomized to Progesterone or placebo.
4. Lipid and BP changes during Progesterone will not differ significantly from those occurring on placebo.

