A two-tailed value of p <0.05 will be considered statistically significant. Statistical analysis will be performed using SAS statistical software for which our lab yearly renews the UBC site license.

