**Significance:**

Many women discontinued estrogen therapy abruptly after the results of the Women’s Health Initiative Study (WHI, 2002) were announced in July, 2002. Most are reluctant to re-start estrogen treatment. They need effective therapy for sleep-disturbing VMS. Preliminary work from our lab has shown in a blinded parallel group trial that was not placebo-controlled that medroxyprogesterone acetate is equally effective as conjugated equine estrogen in the control of VMS. Should Progesterone be shown to significantly improve VMS over placebo (an expected 30-40% placebo response) this would be a major therapeutic advance for women’s health. Progesterone may also be expected to improve vascular function because of previous studies and it is lipid neutral in several trials. Progesterone should not be as likely to concern women because it does not increase venous thromboembolism as estrogen does, is unlikely to cause strokes as it significantly lowers BP, and does not cause abnormal vaginal bleeding or migraine headaches.

If we are able to show improved forearm blood flow after three months of Progesterone therapy this observation would suggest it has important positive vascular effects. We have previously shown that endothelium-dependent forearm blood flow is improved by acute intra-arterial progesterone infusion in physiological luteal phase doses (Mather et al., 2000).

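### Null hypothesis 1 is worded so that a before-after rise in forearm blood flow in the progesterone arm alone contradicts it, beside the comparison with placebo

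*Protocol*

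**What the plan says.** All references are to the protocol.

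- **Null Hypotheses, item 1** (forearm blood flow, FBF): the study drug "will not increase endothelium-dependent forearm blood flow in response to acetylcholine infusion compared with the baseline before therapy or compared with placebo treatment". Two comparators are joined by *or*: the woman's own baseline, and placebo.
- **Null Hypotheses, item 2** (vasomotor symptoms, VMS): progesterone "will cause no change in VMS over time compared with placebo". Placebo is the only comparator.
- **Null Hypotheses, item 4**: "Lipid and BP changes during Progesterone will not differ significantly from those occurring on placebo". Again placebo only. Item 3, on quality of life, is stated as a difference between the randomised groups.
- **Purposes, item 1**: asks whether progesterone "increases forearm blood flow in response to infusion of acetylcholine" and names no comparator.
- **Significance**: "improved forearm blood flow after three months of Progesterone therapy this observation would suggest it has important positive vascular effects". No comparator is named here either, although the VMS sentence in the same section does refer to placebo.
- **Statistical analysis**: FBF is analysed as within-woman change from baseline, changes are to be compared by therapy, and about 25 women per arm are said to be needed. The significance rule is "A two-tailed value of p <0.05 will be considered statistically significant", with no division between comparisons.

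**The concern.** Randomisation protects the contrast between the arms. It does not protect the change within one arm, which adds any drug effect to everything else that differs between two measurements three months apart: familiarity with an invasive two-hour procedure, time trend, technical drift and placebo response.

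As hypothesis 1 is worded, a significant rise in the progesterone arm would contradict the null even if the placebo arm rose by the same amount. The FBF sentence under Significance would then carry that result to a statement about vascular benefit. The endpoint is not a minor one. The Methods section calls change in mean FBF during acetylcholine infusion the primary outcome measure, while the Statistical analysis section gives primary status to VMS.

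**Working it through.** **1. The plan's own figure.** The only number tied to this hypothesis is about 25 women per arm. It cannot be reproduced, because no effect size, SD or power is given for FBF. For scale, a two-sample t-test with 25 per arm at two-sided 0.05 has 80% power for a difference of 0.81 SD of the change score (normal approximation: (1.960 + 0.842) × √(2/25) = 0.79 SD).

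**2. Logic of the wording.** Let A be an increase over baseline in the progesterone arm, and B a larger increase on progesterone than on placebo. Item 1 says that progesterone will not produce A or B, so the null is *neither A nor B*. Either one contradicts it.

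**3. Set-up.**

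- From the protocol: n = 25 per arm, analysis of within-woman change, two-sided 0.05 for each test.
- Assumed: normal change scores with SD 1 in both arms, no drug effect, and a drift δ (in SD of change) common to both arms. The protocol gives no value for δ, so a range is shown.
- Test A: t = mean change on progesterone ÷ (SD/√25), 24 degrees of freedom, critical value 2.064.
- Test B: t = difference in mean change ÷ √((s₁² + s₂²)/25), 48 degrees of freedom, critical value 2.011.

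**4. No drift (δ = 0), by simulation.**

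| Rule | Either direction | Increase only |
|---|---|---|
| Test B alone | 5.0% | 2.5% |
| A or B | 8.3% | 4.2% |

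Two independent tests would give 1 − 0.95² = 9.75%. The true figure is lower because both tests use the same progesterone data. Hypothesis 1 speaks of an increase, so the last column is the one that applies most directly.

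**5. With drift common to both arms, chance of a false increase.**

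| δ (SD of change) | A or B | Test B alone |
|---|---|---|
| 0.1 | 8.0% | 2.5% |
| 0.2 | 16% | 2.5% |
| 0.3 | 30% | 2.5% |
| 0.4 | 48% | 2.5% |
| 0.5 | 67% | 2.5% |

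Nearly all of this comes from test A. Its chance of a significant increase follows from the noncentral t distribution with 24 degrees of freedom and noncentrality δ√25 = 5δ. At δ = 0.3 the noncentrality is 1.5 and the probability 30.2%. At δ = 0.5 it is 2.5 and the probability 67.0%. The drift cancels in test B, which therefore stays at its nominal level.

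**The case against.** The strongest reply is that the planned analysis is between arms. The Statistical analysis section proposes a two-sample, two-tailed t-test (in the VMS calculation), says that all outcomes will be compared as changes within women by therapy, and gives the FBF numbers per arm. Nowhere does the protocol specify a paired or one-sample test in the progesterone arm, or a formal rule that one arm's change counts as success. The Significance section is rationale in hedged language, and the exact test may be fixed in a statistical analysis plan that is not shown.

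Most of this stands. The Statistical analysis section is best read as intending a comparison of changes between arms. But it does not say that this comparison alone decides hypothesis 1, and it does not withdraw the baseline comparator. If a between-arm test was intended, the hypothesis disagrees with the analysis section. It is then a statement in the protocol that needs correcting, not a detail left for later.

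The objector is also right that the drift values have no source in the protocol, that 8.3% counts rejections in both directions, and that the adjustment for the un-infused arm removes some systemic change. It does not remove every retest effect.

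A reader might go further in three ways that the protocol does not support:

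- **That the placebo control is discarded.** The same sentence keeps it as the other comparison.
- **That VMS has the same defect**, because Purposes item 2 asks "whether and by how much day and night VMS will change in response to treatment with OMP or placebo". That phrase describes change from the pre-treatment month. Null hypothesis 2, the two-sample t-test and the Significance section all make VMS a question against placebo.
- **That regression to the mean inflates the FBF change.** Women are selected on VMS. The baseline FBF study follows the establishment of eligibility and is not used to select them.

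**Conclusion.** The point holds as a fault in the wording of hypothesis 1. Its clause "compared with the baseline before therapy or compared with placebo treatment" opens an uncontrolled route to rejecting the null, which is inconsistent with hypotheses 2 to 4 and with the comparison by therapy in the Statistical analysis section. The protocol does not show that an uncontrolled analysis will be used. It leaves one open. Success here means only rejection of null hypothesis 1, since no formal success rule is given.

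The excess error without drift is modest and needs no outside figure beyond normal change scores with equal SD. The larger figures depend wholly on the assumed drift and show how the before-after route behaves. They are not estimates for this trial.

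**What to change.** - **Null hypothesis 1:** remove the baseline comparator and state the null as no difference between progesterone and placebo in the change from baseline in the FBF response to acetylcholine.
- **Statistical analysis:** add one sentence saying that this between-arm comparison decides hypothesis 1 and that within-arm changes are descriptive.
- **Significance:** add the comparison with placebo to the FBF sentence, as the VMS sentence in that section already has.

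The cost is wording only. Sample size, visits and data collection do not change.

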**Design:**

Prospective four-month study with run-in observational month and three months’ randomized double blind placebo-controlled trial (RDBPCT). 125 women will be randomized to active Prometrium (300 mg) or Prometrium Placebo.

**Timeline (see flowchart in Appendix I)**—one month observational study during which they will be determined to be eligible (see below), will record **baseline experiences** on the Daily Menopause Diary [name], 1990). After establishment of eligibility (see below), we will perform the initial forearm blood flow study (FBF, see methods) for assessment of endothelial function.

**Outcome measures:**

1. **Forearm blood flow** prospectively measured before and after three months of therapy.
2. **Vasomotor symptoms** prospectively recorded during the first month compared with changes in months one, two and three of the RDBPCT.
3. **Other hormone-related quality of life** measures on the Daily Menopause Diary, especially self worth, sleep, and energy.
4. **Changes in two published Quality of Life instruments** the Rand SF-36 and the Menopause-specific Quality of Life (MenQoL) questionnaires
5. **Lipid, BP and weight changes**—these will provide new and important therapy effects.

**Participants:**

Menopausal women (final menstrual period one or more but less than 10 years before) without evidence of vascular disease (normal BP, without diabetes mellitus, normal cholesterol levels and non-smoker for at least a year, normal ECG) and with moderate VMS during the day and night. “Moderate VMS” are operationally defined for **daytime** as five flushes of a 1 intensity [on the 0-4 scale], 2-4 of a 2 intensity or 1-2 of a 3 intensity per week. Moderate VSM for **night** are defined as 1 flush of a 2 intensity or 2-3 of a 1 intensity per week.

Exclusion criteria:

Any menstruation in the preceding year.

A women who has had a hysterectomy without ovariectomy unless she is 60 years of age (and therefore could be confidently expected to be menopausal).

Use of ovarian hormone therapy (estrogen, progestin, progesterone or androgen) or SERM therapy (Raloxifene or Tamoxifen) in the preceding six months.

BMI over 35 or less than 20.

Mean of several pre-treatment BPs over 145/95 (supine, at rest, on no therapy).

History of abnormal cholesterol, abnormal fasting capillary glucose or a diagnosis of diabetes mellitus, any history suggestive of angina or having had an abnormal angiogram, ECG or exercise stress tests.

Finally, an abnormal baseline ECG consistent with ischemia or past infarction.

Randomization will be achieved using a random numbers table generated by computer with the code held by the dispensing pharmacy (Lancaster Medical).

All participants will be required to sign informed consent to a protocol approved by the University of British Columbia and Vancouver Hospital ethics review panels.

**Methods:**

**Forearm blood flow**—this is a classical technique called venous occlusion plethysmography (Benjamin et al., 1995) in which forearm blood flow (FBF) is assessed using changes in a strain gauge at the widest forearm points bilaterally during periods of time in which hand arterial blood flow is occluded and venous arm flow is prevented compared with baseline control infusions (Mather et al., 2000).

A brachial arterial needle is in place for 2 hours during this procedure. However, this brachial arterial needle is much smaller than those used for patients in intensive care settings. Both the PI and the plethysmography technician have undergone this procedure, and women (n=27) in a prior study (Mather et al., 2000) found it acceptable.

Impaired endothelial function is a physiological risk factor for cardiovascular disease. Acetylcholine acts in conjunction with endogenously produced nitric oxide (NO) in order to increase blood flow, so the dose-response of forearm blood flow to acetylcholine measures endothelium-dependent control of blood flow.

Women will come to the lab fasting and having had no caffeine or food for 12 hours. Their BP, fasting capillary glucose and lipid profiles will be measured and they will be sent for an ECG. Over the two hour study, standard dose-escalating concentrations of acetylcholine and sodium nitroprusside are infused intrabrachially. Acetylcholine is to assess endothelium- or nitric oxide-dependent FBF changes and sodium nitroprusside is to assess endothelium independent FBF changes. The primary outcome measure is change in mean FBF during acetylcholine infusion adjusted for changes in the opposite, un-infused arm. All plethysmography measurements will be performed twice in each woman—at baseline and after three months’ blinded intervention.

**Daily Menopause Diary**--daily records will be obtained over four continuous months (one month of control data, and three on blinded therapy). Record-keeping using the diary will be taught using the videotape (Daily Perimenopause Diary 1995). Videos will be made available on loan during the study. Records will be reviewed twice during the baseline month to ensure good data collection.

**Statistical analysis:**

All baseline demographic information, Forearm Blood Flow (FBF) data and Daily Menopause Diary and laboratory information will be entered into a database. Data will be cleaned and analyzed before the therapy code is broken. Residuals will be examined for non-normality and, if necessary, will be analyzed using non-parametric statistics.

Numbers calculations:

Vasomotor symptoms are the primary outcome variable for the study, quantified as a composite score of number of VMS multiplied by the intensity during both the day and night (VMS Score). This method has been used by our laboratory in the past (Van Patten et al. 2002), and has also been used extensively by Loprinzi and his colleagues (Sloan et al. 2001). In short trials in about 1000 men and women, they suggest that 50 women per arm are necessary to provide 80% power to detect a 0.58 SD difference using the same standard two-sample, two-tailed t-test that we propose to use, with an alpha level of 0.05 (Sloan et al. 2001). This corresponds to a shift of 3 units of VMS Score per day.

The total sample size for this study is 125. That is made up of 50 women per arm, plus a 25% allowance for those who discontinue or who prove to be ineligible after enrollment.

Although there is no consensus on the clinically meaningful difference for vasomotor symptoms, 3 units of VMS score is a reasonable choice. Using re-sampling techniques from existing data, (68) show that this sample size is adequate to reveal the effects that they have found with a progestin and with non-hormonal agents such as vitamin E and anti-depressants. It is expected that there will be a placebo effect of 30-45 percent—this sample size allows for that expectation.

The forearm blood flow hypothesis requires approximately 25 women per arm. To reduce the numbers, all outcomes will be compared as changes *within* women (rather than cross-sectionally by group) over time, by therapy. Conservatively, we would need to recruit 30/arm to ensure 25 women per arm completing the three-month therapy study.

The mean FBF data (which we expect will be normally distributed) will be expressed as a within-woman change from baseline. The day and night VMS data will be analyzed separately as a product of intensity and the number. Where appropriate, analyses will use parametric methods. If necessary, non-parametric tests will be used for outcome variables that are non-normal. Changes within women over time by therapy will be compared.

A two-tailed value of p <0.05 will be considered statistically significant. Statistical analysis will be performed using SAS statistical software for which our lab yearly renews the UBC site license.

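### Change scores reduce the numbers only above a baseline/follow-up correlation that the protocol does not give; adjusting for baseline would usually be more precise on the same data

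*Protocol*

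**What the plan says.** All of the relevant text is in the protocol's Statistical analysis section.

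- **Scale and reason.** The FBF sizing paragraph states: "To reduce the numbers, all outcomes will be compared as changes" within women, as opposed to a cross-sectional comparison of the groups. The reason given is economy of sample size, and the sentence covers every outcome.
- **FBF.** Mean FBF "will be expressed as a within-woman change from baseline". About 25 women per arm are said to be required, with 30 recruited. No effect size, SD, power or correlation accompanies these figures.
- **Comparison.** The section's analysis paragraph ends: "Changes within women over time by therapy will be compared". No baseline covariate is named.
- **VMS sizing.** Citing a methodological paper on hot flash trials, the protocol says "50 women per arm are necessary to provide 80% power to detect a 0.58 SD difference". The test behind that figure is a two-sided t-test on two independent groups at the 5% level, which the trial intends to adopt as well. In raw units: "This corresponds to a shift of 3 units of VMS Score per day". The protocol does not say whether the SD is that of an end value or of a change.

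Baselines are collected in any case. The Methods section provides for FBF before and after treatment and for one untreated diary month. The Appendix I flowchart lists quality of life, weight and BP at enrolment and at the end, and lipids at both laboratory visits.

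**The concern.** Subtracting the baseline removes stable differences between women but adds the noise of a second measurement. Which effect is larger depends on how strongly baseline and follow-up are correlated. The protocol states the saving as a fact and omits the one quantity that decides it.

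A change score is also a special case of baseline adjustment, with the slope on baseline fixed at 1. Letting the data estimate the slope usually gives a smaller standard error from the same measurements. This matters most for FBF, where the groups are small, each measurement needs a two-hour brachial arterial procedure, and the efficiency claim is the only support offered for keeping the number low.

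**Working it through.** **Inputs.** From the protocol: 0.58 SD, 3 units per day, 50 per arm, 80% power, two-sided alpha 0.05, and about 25 per arm for FBF. Assumed, because not stated: the correlation rho, shown at 0.3, 0.5 and 0.7, and the ratio of follow-up SD to baseline SD, k, taken as 1 unless varied.

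**1. The protocol's own figure.** The normal approximation gives 2 × (1.960 + 0.842)² / 0.58² = 46.7, so 47 per arm. The noncentral t gives 48. Power at 50 per arm is 82%, so the stated 50 is reproduced to within 2. The implied SD is 3 / 0.58 = 5.17 units. The FBF figure of 25 cannot be reproduced, since it has no inputs.

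**2. Variances with equal SDs**, relative to the end-value variance:

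- end value: 1
- change: 2(1 − rho)
- ANCOVA: 1 − rho²
- ANCOVA / change: (1 + rho) / 2

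Change beats end value only when 2(1 − rho) < 1, that is rho > 0.5.

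**3. Illustration for VMS**, *conditional on 0.58 SD being an end-value SD*. The end-value t-test needs 48 per arm and has 82% power at 50 per arm, whatever rho is.

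| rho | Variance: change | Variance: ANCOVA | Ratio | n per arm, change / ANCOVA | Power at 50 per arm, change / ANCOVA |
|---|---|---|---|---|---|
| 0.3 | 1.40 | 0.91 | 0.65 | 67 / 44 | 68% / 85% |
| 0.5 | 1.00 | 0.75 | 0.75 | 48 / 36 | 82% / 91% |
| 0.7 | 0.60 | 0.51 | 0.85 | 29 / 25 | 96% / 98% |

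**4. Unequal SDs.** In units of baseline variance, the end value has k², change has k² + 1 − 2·rho·k, and ANCOVA has k²(1 − rho²).

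- Change beats end value only if rho > 1/(2k), that is SD at baseline / (2 × SD at follow-up). At k = 0.8 the threshold is 0.625.
- Change minus ANCOVA is (1 − rho·k)². This is never negative, and it is zero when the baseline slope rho·k equals 1. Example: at k = 1.25 and rho = 0.8, change is 1.5625 + 1 − 2 = 0.5625 and ANCOVA is 1.5625 × 0.36 = 0.5625, so there is no gain.
- The ANCOVA / change ratio at rho 0.3, 0.5 and 0.7 is 0.50, 0.57 and 0.63 for k = 0.8, and 0.78, 0.89 and 0.98 for k = 1.25.

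**5. Price of estimating the slope.** The ANCOVA variance is inflated by about 1 + 1/(N − 4), with N the total number of women. With equal SDs the break-even correlation is (N − 5)/(N − 3): 45/47 = 0.957 for 50 women and 95/97 = 0.979 for 100. Simulation at 25 per arm (20,000 trials per setting) gave variances of 1.388 (change) and 0.928 (ANCOVA) at rho 0.3, and 0.0401 and 0.0405 at rho 0.98.

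**6. FBF, in relative terms only.** If 25 per arm was derived for end values, change scores need 25 × 1.40 = 35, 25 × 1.00 = 25 or 25 × 0.60 = 15 at rho 0.3, 0.5 and 0.7. If it was derived for change scores, ANCOVA needs about 25 × 0.65 = 16, 25 × 0.75 = 19 or 25 × 0.85 = 21.

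**The case against.** The best counter-argument is that the protocol names a response scale rather than an unadjusted model. A regression of change on treatment and baseline gives the same treatment estimate as ANCOVA on the follow-up value, and an analysis plan that is not shown might specify it. It is also true that the t-test is named only in the VMS sizing paragraph. So the protocol's wording can accommodate the remedy. What remains is that the protocol does say "using the same standard two-sample, two-tailed t-test that we propose to use", names no covariate for any outcome, and gives a reason for change scores that it does not support.

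Three stronger readings are tempting, and the documents do not support them.

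- *Change scores always lose precision.* They lose nothing when the baseline slope is 1, and in small samples they are marginally better at very high correlations. Above the threshold correlation they do save women against end values.
- *The VMS comparison has only 68% power.* That figure needs rho = 0.3, equal SDs and 0.58 SD being an end-value SD, none of which the protocol states. If 0.58 SD is the SD of a change, the change-score t-test has about 82% power at 50 per arm whatever rho is.
- *Selecting women on the run-in month that also serves as baseline biases the comparison.* Regression to the mean acts alike in both randomised arms. Change score and ANCOVA estimate the same treatment effect without bias.

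**Conclusion.** The point holds as a matter of efficiency. The stated reason for change scores is true only above a threshold correlation: 0.5 with equal SDs, higher if the SD falls on treatment. The protocol gives no value to judge it by. In large samples, baseline adjustment on data already collected is never less precise. With equal SDs and assumed correlations of 0.3 to 0.7 it cuts the variance by 35% to 15%. The exceptions are a slope of 1 (no gain) and, at about 25 per arm, a correlation above roughly 0.96 (a trivial loss).

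The size of the gain in this trial is unknown, because the correlation and the FBF SD and effect are not stated. The VMS power figures are illustrative. The planned analysis would be valid, and nothing here shows that the trial is too small.

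**What to change.** In the Statistical analysis section:

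1. For each continuous outcome, compare the arms by a linear model of the follow-up value (or, equivalently, the change) on treatment, with that woman's baseline value as covariate. Report the adjusted difference and its 95% confidence interval. Unadjusted changes can stay as description.
2. Leave the protocol's outcome definitions and time windows as they are: day and night VMS separately, months one, two and three against the baseline month, and FBF at three months corrected for the arm that is not infused. Changing these would change what is estimated, and this point gives no reason to do so.
3. Keep the non-parametric fallback for non-normal residuals in a form that retains the baseline, for example rank-based ANCOVA.
4. Delete the opening clause of "To reduce the numbers, all outcomes will be compared as changes", or state the correlation it assumes and its source. Also say whether 0.58 SD refers to an end value or a change.

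The cost is one degree of freedom per model and a little analysis work. No new data, visits or participants are needed.
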